### Trial design {8}

This study will include a single-blind, 3-arm, parallel design, randomized superiority controlled trial with a distribution ratio of 1:1:1. Eligible patients will be randomly assigned to the conventional treatment group, single target stimulation group, or dual target stimulation group and will receive intervention treatment for 4 weeks each. This research protocol follows the SPIRIT reporting guidelines [8], as shown in Fig. 1.

**Fig. 1 Fig1:**
[figure not shown]
SPIRIT reporting guidelines

## Methods: participants, interventions and outcomes

### Study setting {9}

This study will be conducted at Shanghai Herson Rehabilitation Hospital (Shanghai, China). It is an affiliated hospital of Shanghai University of Medicine &Health Sciences, with a building area of approximately 32,000 m^2^. Approximately 1000 patients with post-stroke cognitive impairment receive treatment annually. Eligibility screening will be shown on patients with post-stroke cognitive impairment in the ward from December 2022 to October 2023; 57 patients will participate in this trial.

### Eligibility criteria {10}

Researchers will conduct eligibility screening based on inclusion and exclusion criteria. All participants should sign an informed consent form after qualification confirmation.

Inclusion criteria:Male or female patients between 18 and 75 years of age;Right-handed;Patients who meet the diagnostic criteria for vascular cognitive impairment reported in the Guidelines from the Vascular Impairment of Cognition Classification Consensus Study [9] and the Chinese vascular cognitive impairment guideline 2019 [10];The patient should have a clear consciousness and stable vital signs. They should also be able to express themselves and understand instructions to a certain extent. At least one limb should be movable without any issues, and the patient must be willing to participate in cognitive assessments and related training actively;The patient had no cognitive impairment before the onset of the disease but had mild to moderate cognitive impairment after the stroke. They had a primary school education level or above, with a score of 9 < MMSE < 27 and a score of 9 < MoCA < 26;No mental illness, no severe aphasia or hearing comprehension disorders; andVoluntary participation and signing the informed consent (signed by the patient or the authorized person).

Exclusion criteria:Cognitive impairment due to primary or secondary neurological disease, such as normal cranial pressure hydrocephalus, frontotemporal dementia, Parkinson’s disease, multiple sclerosis, encephalitis, and delirium;Accompanied with severe mental, intellectual disabilities, or visual and auditory dysfunction, unable to cooperate in completing various functional evaluations;Cognitive impairment due to depression, schizophrenia, bipolar disorder, psychotic disorder, vitamin D deficiency, toxicosis, or else systematic diseases;Drug/alcohol abuse/dependence within the last 3 months of the first recognition of impairment;rTMS treatment contraindications such as epilepsy patients, pregnant or lactating women, or with a metal or electric implanted device (e.g., deep brain stimulator, ventriculoperitoneal shunt, aneurysm clip, pacemaker, cochlear, surgical staples on the scalp);MRI contraindications (such as metal implants or claustrophobia); andParticipating in concurrent pharmacological or nonpharmacologic treatment research.

### Who will take informed consent? {26a}

To determine eligibility for the study, neurologists will evaluate patients who meet the criteria mentioned above. Patients who meet the eligibility criteria will receive initial research details from their doctor and researchers. If they agree to participate, they will be given written information outlining the study's objectives and procedures, and they will sign an informed consent form.

### Additional consent provisions for collection and use of participant data and biological specimens {26b}

The informed consent form indicates that they are asked to cooperate with the investigators for scale assessment, TCD, and blood collection at baseline and after 4 weeks. The patient is informed that all their personal information in the study will be kept strictly confidential. Due to work needs, it shall only be used for the research group members and the research unit's ethics committee. The personal data of these patients will be archived in numbered form, and names and identities will not be exposed or disclosed.

## Interventions

### The explanation for the choice of comparators {6b}

All patients will receive routine rehabilitation treatment (40 min per day, 5 days per week, for 4 weeks), with one-on-one physical and occupational therapy provided by qualified rehabilitation therapists.

### Intervention description {11a}

#### rTMS protocol

The rTMS treatment uses a magnetic stimulator with an 8-shaped coil (MagProX100, Denmark). Participants were divided into three groups: the sham stimulation group, the single-target stimulation group, and the dual-target stimulation group. After recruiting PSCI patients, they were randomly assigned to one of three groups for 20 treatment courses (4 weeks, 5 consecutive days, and 2 days off per week). During the sham stimulation, the “8” shaped coil was placed at a 90° angle to the scalp. The rTMS treatment of the three groups will be completed by a qualified therapist with over 5 years of work experience from the Neurocontrol Room of Shanghai Herson Rehabilitation Hospital.

The detailed information on parameters and grouping were as follows:Group 1: sham rTMS over left DLPFC+ ipsilesional M1Group 2: left DLPFC+sham rTMS over ipsilesional M1Group 3: left DLPFC+ ipsilesional M1Left DLPFC: 10 Hz, 80% RMT, 2000 pulses (5s×40 trains,25s interval)Ipsilesional M1: 10 Hz, 80% RMT, 1200 pulses, (2s×60 trains, 8s interval)

#### RMT

The resting motor threshold (RMT) is the lowest stimulation intensity to induce at least 50% of the time in a finite number of trials (typically 10).

The RMT was determined as the minimum stimulating power necessary to elicit an overt motor response (motor evoked potential, MEP, more significant than 50 μV) in the contralateral side abductor pollicis brevis (APB) at least 5 of 10 times [11].

#### Localization of stimulation site

The MagPro X100 instrument uses an “8” stimulation coil for transcranial magnetic stimulation in the cortical area, which can collect muscle potential activity. By applying a single pulse stimulation at a higher intensity and moving the coil, the abducts polis MEP > 50 uV can be located and marked as the best stimulation point using a marker. The DLPFC region is targeted for stimulation using the “standard 5 cm” method, which involves translating 5 cm forward from the left M1 region [12].

#### Criteria for discontinuing or modifying allocated interventions {11b}

Patients who wish to stop participation;Patients who could not undergo the baseline assessment;Patients who did not complete the rTMS treatment sessions; andPatients who suffered from worsening symptoms.

### Strategies to improve adherence to interventions {11c}

To improve the patient's adherence to the intervention protocols, once every rTMS session was completed, a predesigned treatment record card should be filled and signed by the rTMS therapists and the patients or their authorized persons and ultimately returned to the study researchers. The specialized physiotherapists in our center will monitor adherence to the rehabilitation protocol after rTMS. They are in close contact with the treating physiotherapists and monitor progression during study visits.

### Relevant concomitant care permitted or prohibited during the trial {11d}

The route of medical care based on the individualized illness for each patient is permitted, but medications for improving cognition, such as Pfizer’s Aricept, will be prohibited during the trial.

### Provisions for post-trial care {30}

Throughout the entire research process, there is no harm to participants.

### Outcomes {12}

This study measures the effectiveness of rTMS treatment on cognitive ability. Two primary assessments will be conducted, the Montreal Cognitive Assessment Beijing Version (MoCA-BJ) and the Mini-Mental Status Examination (MMSE). In addition, secondary assessments such as the modified Barthel index (MBI), Trail-Making Test (TMT), digital span test (DST), transcranial Doppler (TCD) examination, and serum BDNF and VEGF levels will also be conducted. All assessments will be done twice, pre-treatment (baseline) and post-treatment. A trained neuropsychologist will conduct all cognitive assessments without informing the participants’ cognition status.MoCA-BJ. The MoCA-BJ scale is one of the Chinese versions of the Montreal Cognitive Assessment used to assess general cognitive function [13], which has high sensitivity and specificity for screening cognitive impairment from patients with stroke [14]. The cognitive function was evaluated through alternating connections, drawing cubes, drawing clocks, naming, retelling, subtracting seven from 100, and directional ability. This scale was developed based on MMSE, with a score of 30 points and ≥ 26 points representing normal cognition [15]. A patient’s cognitive function is better if their score is higher.MMSE. The MMSE is a quick and easy cognitive function screening tool commonly used in clinical settings. It takes about 10 min to complete and consists of a single-page, 30-point test that assesses various cognitive domains including memory, attention, and language. A higher score indicates better overall cognitive function, with a score of 27–30 indicating normal function, 21–26 indicating mild impairment, 10–20 indicating moderate impairment, and 0–9 indicating severe impairment [16].TMT(Chinese version). In the TMT-A section, connect the numbers from 1 to 25. TMT-B includes numbers in square and circular shapes, requiring participants to arrange the two forms alternately when connecting numbers in sequence. The scoring criteria are the time taken to complete TMT-A and TMT-B, as well as the interference amount (TMT-B time consumption minus TMT-A time consumption) [17]. This tool is commonly used for diagnosing visual attention, executive function, and processing speed in neuropsychological diseases [18, 19].ADL. The primary activities of daily living are assessed with the modified Barthel Index (MBI) [20], which is used to evaluate individual self-care performance and derived from the Barthel Index. In this study, we used the Chinese version of MBI [21]; it also consists of ten items: personal hygiene, bathing, feeding, toileting, stair climbing, dressing, bowel control, bladder control, ambulation or wheelchair and chair-bed transfer with total 100 scores indicating completed independence. A higher score on the MBI indicates superior independent living ability [22].DST. The scale can be divided into digit span forward (DSF) and digit span backward (DSB), each of which consists of two sets of 2-digit to 10-digit tables. The test begins with item 1 and is stopped after two incorrect attempts. The total score of the DSF and DSB indicates the participant’s attentional functioning, with a higher score indicating better function. A score of less than 5 suggests impaired attention function [23].TCD. According to the latest epidemiological survey, cerebrovascular disease and its risk factors are significant contributors to cognitive decline. By managing these risk factors, it is possible to delay cognitive decline [24]. TCD can assess large vascular lesions and cerebrovascular function, which can provide a basis for early diagnosis and treatment of PSCI [25]. The main indicators for assessment are the average blood flow velocity (Vm), pulsatile index (PI), and resistance index (RI) of the patient’s middle cerebral artery, which measure cerebral hemodynamic changes.Blood sampling. Serum samples will be obtained to analyze BDNF and VEGF levels at baseline and post-treatment. Peripheral venous blood (5 ml) will be collected from 7:00 am to 9:00 am in a climate-controlled room following overnight fasting [26]. The blood was then centrifuged to separate the serum and stored at -80℃ in a refrigerator. Serum levels of BDNF and VEGF will be measured using enzyme-linked immunosorbent assay (ELISA) kits. The steps were followed according to instructions [27]. All samples will be measured by the same technician who is blinded to the patient treatment status. All samples will be evaluated in duplicate and averaged.

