**Methods:**

A single-center, single-blind, randomized controlled trial will be conducted, and fifty-seven PSCI patients will be recruited and randomly assigned to one of three groups based on the stimulating site. The primary outcome is cognitive function, measured using the Montreal Cognitive Assessment Beijing Version (MoCA-BJ) and Mini-Mental Status Examination (MMSE). The secondary outcomes are the modified Barthel Index (MBI), Trail-Making Test (TMT), and digital span test (DST). Furthermore, changes in brain activity are assessed using transcranial Doppler sonography (TCD) examination and serum levels of brain-derived neurotrophic factor (BDNF) and vascular endothelial growth factor (VEGF) closely related to nerve and vascular repair after brain injury. All outcomes will be measured at baseline and 4 weeks after treatment.

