**Discussion:**

If dual-target rTMS in significant improvements in cognitive function, this method could be considered as a first-line clinical treatment for PSCI. This proposed study has the potential to identify a new, evidence-based intervention that can enhance cognition and independent living in patients with cognitive impairment after stroke.

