### Sample size {14}

The study's sample size is based on the expected difference in outcome measure of the MMSE score between the two intervention groups. We determined this effect by reviewing the literature on repetitive transcranial magnetic stimulation's impact on stroke patients [28]. We used a 1:1:1 ratio between groups and calculated the power using G*Power free software (Version 15.0.5). In addition, considering the insufficient sample size caused by patient detachment during the research process, it is necessary to expand the sample size by 20%, resulting in a total sample size of 57 patients.

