## Statistical methods

### Statistical methods for primary and secondary outcomes {20a}

Statistical analysis will be conducted using SPSS version 25.0 and Microsoft Excel 2016 software.

Measurement data (e.g., MoCA BJ, MMSE, TMT, DST, MBI, BDNF, and VEGF levels in serum, TCD) were statistically described by mean ± standard deviation (*x* ± *s*); count data (such as stroke type, hemiplegic side, and stroke risk factors) were described by frequency (*n*) and percentage (%). The measurement data were first tested for normality, and those not conforming to the normal distribution were expressed by M (P25, P75) and analyzed by Kruskal–Wallis H test; the data conforming to the normal distribution were expressed by *x* ± *s*, one-way analysis of variance was used for comparison between multiple groups, LSD-t-test, and paired *t*-test was used for patients before and after treatment. All test levels were significant at *α* = 0.05 and *P* < 0.05.

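### Two primary scales are each tested at 0.05 with no rule for success; if either scale is enough, the false-positive rate is about 8–9%

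*Protocol article*

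**What the plan says.** The Methods paragraph of the abstract describes one construct measured by two instruments: "The primary outcome is cognitive function, measured using the Montreal Cognitive Assessment Beijing Version (MoCA-BJ) and Mini-Mental Status Examination (MMSE"). The Outcomes section lists them as two assessments: "Two primary assessments will be conducted, the Montreal Cognitive Assessment Beijing Version (MoCA-BJ) and the Mini-Mental Status Examination (MMSE"). Neither place says how the two results combine into one conclusion.

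The Trial design section describes a "3-arm, parallel design, randomized superiority controlled trial with a distribution ratio of 1:1:1", so each scale has three pairwise contrasts. The statistical methods section plans, for normally distributed data, "one-way analysis of variance was used for comparison between multiple groups, LSD-t-test", and sets one level throughout: "All test levels were significant at *α* = 0.05 and *P* < 0.05". It describes no adjustment for multiplicity.

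The Sample size section says the "sample size is based on the expected difference in outcome measure of the MMSE score between the two intervention groups". The Discussion paragraph of the abstract states what a positive trial would mean: "If dual-target rTMS in significant improvements in cognitive function, this method could be considered as a first-line clinical treatment for PSCI". That sentence names neither a scale nor a comparator.

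**The concern.** A flat 0.05 on each of two primary scales holds the error of the overall conclusion at 5% only if both scales must be significant. If one is enough, the trial has two chances to succeed by luck. The article leaves this open, so the choice could be made after the results are seen.

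The claim at stake is a strong one: that dual-target stimulation could become a first-line treatment. A reader will take 0.05 as the error rate behind it. Under the either-scale reading it is not.

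**Working it through.** **Plan's own figure.** The article states no overall error rate, only 0.05 per test, so there is none to reproduce.

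**Inputs from the article.** Two primary scales (Outcomes). Three arms at 1:1:1 (Trial design). 57 patients, so 57/3 = 19 per arm, which matches the number blocks in the Implementation section. Level 0.05 for every test (statistical methods).

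**Assumptions.** Tests are two-sided, since sidedness is not stated. Data are normal, which is the ANOVA branch; the Kruskal–Wallis branch names no pairwise test and is not covered. The correlation ρ between the scales is not in the article; 0.5–0.8 is taken as the working range and 0–0.9 as the wide one. There is no true difference between arms on either scale.

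**Step 1: one scale.** With three arms, LSD tests done only after a significant F-test hold 5% within a scale. Simulated: 5.0%. On this reading the three pairwise tests add nothing, and any excess comes from having two scales.

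**Step 2: bounds for two scales.** P(either) = 0.05 + 0.05 − P(both). If the scales were independent, this is 1 − 0.95² = 9.75%. If they always agreed, it would be 5%.

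**Step 3: simulation.** 200,000 trials per setting, 19 per arm, pooled-variance F and t tests. The Monte Carlo standard error near 8% is √(0.08 × 0.92 / 200,000) = 0.06 percentage points. Results in per cent:

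| ρ | F-gated LSD, either scale | Dual vs single at 0.05, either scale | Ungated LSD, either scale | F significant on both scales | Dual vs single at 0.025, either scale |
|---|---|---|---|---|---|
| 0 | 9.7 | 9.7 | 22.6 | 0.2 | 5.0 |
| 0.5 | 9.1 | 9.0 | 21.2 | 0.8 | 4.6 |
| 0.6 | 9.0 | 8.9 | 20.5 | 1.1 | 4.6 |
| 0.7 | 8.4 | 8.3 | 19.4 | 1.5 | 4.3 |
| 0.8 | 8.0 | 7.9 | 18.3 | 2.0 | 4.1 |
| 0.9 | 7.2 | 7.1 | 16.5 | 2.8 | 3.6 |

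The dual-versus-single columns test that contrast directly, without an F-test gate. With 15 per arm the results are the same within simulation error, so arm size is not what drives them.

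**Step 4: consistency check.** At ρ = 0.5, 0.05 + 0.05 − 0.008 = 9.2%, against 9.1% simulated. At ρ = 0.8, 0.05 + 0.05 − 0.020 = 8.0%, against 8.0% simulated.

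**Step 5: the fix.** When neither scale has a true effect, Holm makes a false claim only if the smaller p-value passes 0.025. The ceiling is 0.025 + 0.025 = 5%. The last column gives 4.1–4.6% for ρ of 0.5–0.8.

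**The case against.** The strongest reply is that the either-scale rule is an inference. The abstract speaks of one outcome measured by two instruments, which can be read as requiring both. On that reading the error is 0.8–2.0% with F-tests on both scales, well under 5%. This stands, and it is why the 8–9% must be stated as conditional. It does not remove the gap, because nothing in the article commits to the both-scales reading.

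A second reply is that a condensed article may leave such rules to an analysis plan. That carries weight for details such as whether LSD follows a significant F-test. It carries less here, because the article itself fixes two primaries and one unadjusted level for all tests. An analysis plan that split alpha would depart from that statement.

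Three stronger readings are tempting, and the article does not support them:

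- **An error rate of 18–21%.** This needs LSD to be run regardless of the F-test. The article does not state the gate, but it lists LSD directly after the analysis of variance, and the ordinary reading is that LSD follows a significant F.
- **Any one of six comparisons can carry the conclusion.** The abstract's aim compares dual target with single target and with usual care, and its conclusion concerns dual target only. Single target versus control cannot support it. That leaves at most 2 scales × 2 contrasts = 4. The sample size wording most naturally points to dual versus single.
- **MMSE is already the lead scale, so the article contradicts itself.** Sizing a trial on one of two primaries is not a contradiction, and the Sample size section does not rank the scales.

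**Conclusion.** The point holds in conditional form. If a significant result on either scale counts as success, the false-positive rate of the primary conclusion is about 8–9% with LSD gated on the F-test, and about the same for dual versus single target tested alone. This rests on normal data, two-sided tests and an assumed correlation of 0.5–0.8; every correlation from 0 to 0.9 gives more than 5%. If both scales were required, the rate would be below 5%. The paired before–after tests within arms are not counted.

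The defect is the absent success rule alongside a flat 0.05. It should be fixed because it bears on the main claim and cannot be repaired credibly after the results are known. The conditional size and the simple remedy do not justify ranking it higher.

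**What to change.** Before unblinding, amend the protocol and update the registry entry to:

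- name dual versus single target at W5 as the confirmatory contrast, tested directly on each scale;
- keep MoCA-BJ and MMSE both primary and apply Holm across them: the smaller p-value against 0.025 and, if it passes, the larger against 0.05;
- label the other pairwise contrasts secondary, with LSD only after a significant F-test;
- tie the conclusion in the abstract's Discussion paragraph to the confirmatory contrast.

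**Cost.** Each scale loses some power because the first step is at 0.025. The loss cannot be quantified from the article, which gives no effect size, standard deviation or power. Dual target versus usual care, the other half of the abstract's aim, becomes secondary. The Trial status section says recruitment is under way, so this is a formal amendment and not an edit of wording.

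**Alternatives the sponsor may prefer.** Requiring significance on both scales needs no alpha split and keeps both primary, but lowers power. Making MMSE the sole primary matches the scale used for sizing, but demotes MoCA-BJ, which the Outcomes section credits with good accuracy for detecting cognitive impairment after stroke. Either closes the gap if the confirmatory contrast is also named.

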
### Participant timeline {13}

This study will start with the eligibility screening of subjects. Once the eligibility for participation is confirmed, the patient will sign an informed consent form and be randomly assigned to one of the three groups. We will evaluate their clinical scale, perform TCD, and conduct serological tests at the beginning (W0) and after 4 weeks of rTMS treatment (W5). We will keep track of the number of participants who were excluded, refused consent, or withdrew from the study and the reasons why. The SPIRIT plan is shown in Fig. 2.

